## **PROJECT 2: Regression of Cerebral Vascular Disease in Severe OSAS using CPAP Therapy**

**Hypothesis:** *Early changes of cerebral microvascular disease (indicated by retinal abnormalities) and macrovascular disease (indicated by carotid atherosclerosis and IMT) present in patients with severe OSAS will regress following 12 months treatment with nasal CPAP therapy.*

**Design:** This will be a one-year prospective, longitudinal, observational study of OSAS patients (acting as their own controls). Following discussion with our Ethics Committee, it would not be acceptable to have a randomised, controlled design with a sham treatment arm over a one year period for patients with severe, symptomatic OSAS.

**Subjects:** We will recruit 80 patients from Project 1 (40 in year 1 and 40 in year 2), who have been diagnosed with severe, symptomatic OSAS (RDI >30 events/hr, ESS >9). Exclusion criteria are as for Project 1, plus current smoking or an inability to tolerate CPAP therapy. Successive patients from Project 1 who meet the inclusion criteria will be approached to participate. Over the first two years, our laboratory will diagnose over 400 patients who meet the inclusion criteria.

**Baseline/Anthropometry Data:** Same as for Project 1.

**Procedures:** PSG, Carotid Artery Ultrasound, Retinal Photography as for Project 1.

**Protocol:** Recruited subjects (n=40/year for first 2 years) will complete a run-in period, with review of clinical history, blood lipids, and blood pressure to ensure that subjects have been stabilised on optimal standard therapy for cardiovascular risk factors (normal values with no clinically significant changes). Optimal standard therapy will include continued non-smoking, maintenance of weight, medication (as required) to keep daytime blood pressure and blood lipid profile normal. When clinically stable, diagnostic PSG with repeat carotid Doppler ultrasound (pm) and retinal photography (pm and am) will be performed as a baseline. Subjects will then have a laboratory CPAP titration study, to eliminate snoring and obstructive events as per laboratory protocol.

**The study treatment period will run for 12 months, with monthly monitoring of CPAP compliance** (machine hours at pressure recorded), regular study co-ordinator follow up, and continued monitoring and treatment of cardiovascular risk factors. Subjects will be stratified during analysis according to medication use for cardiovascular risk factors and CPAP compliance.

**Overnight CPAP review studies using the patient's CPAP treatment pressure will be undertaken at 6 months and one year.** Repeat carotid Doppler ultrasound (pm), retinal photography (pm and am), blood pressure (pm and am), fasting blood lipids and sugar, and weight will be measured.

**This duration of study is adequate to detect clinically relevant outcomes.** An increase in IMT of >0.03 mm/year is detectable and clinically relevant, as it is associated with a doubling in incidence of coronary events (44). We anticipate a reduction of at least this amount (15). For retinal photography, a decrease in 3.5  $\mu$ m/year of arteriolar calibre is detectable, measurable in a one year time frame, and associated with a 10 mmHg increase in mean arterial blood pressure (31), making it clinically relevant. Both arteriolar narrowing and venular widening are predictive of stroke (59).

**We have chosen to compare the same subjects before vs after the intervention but not to have an untreated control arm in this study** due to efficiency of paired comparison and the well recognised ethical problems with not treating severe OSAS. This will enable a valid paired comparison with the differences between the before and after treatment measures being related to the treatment intervention over 1 year. The primary outcome variables (CRAE, CRVE, AVR and IMT) are objective measures of structural changes which are unlikely to spontaneously improve without intervention, or be affected by a placebo type response.

***We acknowledge that compliance with CPAP treatment will be a critical factor to the success of this trial.*** Patients will be offered as much support as required in the initial phases of the trial by the study co-ordinator, with four weekly review throughout the study. Patients will be able to contact the study co-ordinator at any time to resolve problems. CPAP compliance will be monitored objectively by nights and hours of use from machine downloads at study visits, together with compliance with routine medication(s). We will target a minimum compliance of 4 hours per night.

**Statistical Analysis and Sample Size:** Power analysis is based on data relating to the observed reduction in IMT during CPAP therapy (15). Power calculations show that with a **sample size of 64** we will have 80% power to detect a difference in IMT of 0.025 mm over 12 months, assuming that the common standard deviation is 0.050 mm and using a two group t-test with a 0.05 two-sided significance level. Given the demonstrated reduction in IMT of 9% (0.063 mm) in 24 patients over only four months of CPAP treatment (15), we believe that our power calculation is quite conservative, and that our sample size is robust. Similarly, following 12 months of treatment for hypertension, there have been demonstrated improvements in retinal vessel diameter of 12.5% (24), consistent with the changes in IMT. We will study 80 subjects to allow for a 20% drop-out rate.

**Significance:** A reduction in atherosclerosis (decrease in IMT) and retinal microvascular changes (increase in CRAE, decrease in CRVE) will be related to CPAP therapy, as other cardiovascular risk factors will be stable over the study period, and any other functional changes will be adjusted for during analysis. ***This study will determine if CPAP treatment in patients with severe OSAS results in regression of both cerebral microvascular and macrovascular disease,*** implicating OSAS as a pathogenic factor in cerebral vascular disease, and implying a possible role for treatment of OSAS in risk reduction from cerebral vascular disease.

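### Project 2 records CPAP use as continuous machine hours, but the only analysis use stated is stratification, which weakens the study's one between-patient CPAP comparison

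*Protocol*

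**What the plan says.** All references are to Project 2 of the Protocol unless stated.

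- **Data.** The paragraph on the 12-month treatment period describes monthly compliance monitoring ("machine hours at pressure recorded"). The paragraph on compliance adds: "CPAP compliance will be monitored objectively by nights and hours of use from machine downloads at study visits".
- **Analysis.** The treatment-period paragraph continues: "Subjects will be stratified during analysis according to medication use for cardiovascular risk factors and CPAP compliance". The number of strata, the boundaries, and whether the two factors are crossed are not stated. The Statistical Analysis and Sample Size paragraph does not mention hours.
- **Target.** "We will target a minimum compliance of 4 hours per night". This is the only compliance threshold in the document, and it is not called a stratum boundary.
- **Design.** The investigators chose to "compare the same subjects before vs after the intervention but not to have an untreated control arm in this study".
- **Size.** With a "sample size of 64", "we will have 80% power to detect a difference in IMT of 0.025 mm over 12 months"; and "We will study 80 subjects to allow for a 20% drop-out rate".
- **Contrast with Project 1.** Its Statistical Analysis and Sample Size paragraph enters OSAS and snoring severity as continuous predictors in linear regression, and states power for a correlation.

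**The concern.** A before-after change in one treated group cannot separate CPAP from time, or from the cardiovascular treatment that continues through follow-up. If CPAP drives the change, patients who use it for more hours should change more. Project 2 has no other between-patient evidence of this kind, and the protocol itself regards compliance as decisive for the trial's success.

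Strata treat everyone within a band as equally exposed. With a 4-hour boundary, 0.5 and 3.9 hours count as the same exposure, as do 4.1 and 8 hours. A real dose-response in IMT, CRAE, CRVE or AVR could then be missed, although the finer measurement is already on file. The protocol gives no reason for grouping here after using continuous exposure in Project 1.

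**Working it through.** **1. The plan's own figure.** For two groups, difference 0.025 mm, SD 0.050 mm, two-sided 0.05 and 80% power:

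n = 2 × (1.960 + 0.842)² × (0.050/0.025)² = 2 × 7.85 × 4 ≈ 63 per group; the exact t-test gives 63.8, so 64. Then 64/0.80 = 80.

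The stated 64 therefore reproduces, but as a per-group number, while the design has 64 completers in total. For the present point, what matters is that 0.050 mm is labelled a common SD for a two-group test. Using it as the SD of change is an assumption, relaxed in step 5. On that assumption, the paired comparison in all 64 has 97.6% power for 0.025 mm.

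**2. Information kept when hours are cut.** For normally distributed hours cut at proportion p, the share kept is φ(z_p)² / [p(1 − p)].

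| Grouping | Kept | Lost |
|---|---|---|
| 50/50 | 0.3989²/0.25 = 64% | 36% |
| 30/70 | 0.3477²/0.21 = 58% | 42% |
| 25/75 | 0.3178²/0.1875 = 54% | 46% |
| 20/80 | 0.2800²/0.16 = 49% | 51% |
| Tertiles, trend | 79% | 21% |
| Quartiles, trend | 86% | 14% |

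**3. Power at 64 completers, by correlation r between hours and change.** Cutting multiplies r by the square root of the share kept (noncentral t, two-sided 0.05).

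| r | Continuous | 50/50 | 30/70 | Tertile trend |
|---|---|---|---|---|
| 0.25 | 53% | 36% | 33% | 44% |
| 0.34 | 81% | 60% | 56% | 71% |
| 0.40 | 93% | 76% | 71% | 85% |
| 0.50 | 99.5% | 93% | 90% | 97.5% |

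**4. Power on the scale of the outcome.** The protocol gives no distribution of hours, so these are assumptions: normal hours, clipped to 0–9; IMT reduction proportional to hours; change SD 0.050 mm; half of patients on medication, entered as a covariate. Mean reductions are 0.025 mm (design effect), 0.050 mm, and 0.063 mm (the cited four-month CPAP study). Simulation with 20,000 runs per cell; entries are continuous / 4-hour split / tertile trend, in %.

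| Hours, mean/SD | 0.025 mm | 0.050 mm | 0.063 mm |
|---|---|---|---|
| 4/2 | 46/32/38 | 96/84/91 | 100/95/98 |
| 4.5/2 | 39/26/32 | 91/74/83 | 98/90/95 |
| 5/2 | 33/22/28 | 85/62/76 | 96/80/91 |
| 5/1.5 | 21/14/18 | 63/38/53 | 82/55/72 |
| 5.5/2 | 27/17/22 | 76/49/66 | 92/67/85 |

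Example for 4.5/2 at 0.050 mm: slope = 0.050/4.5 = 0.0111 mm per hour; r = (0.0111 × 2)/√[(0.0111 × 2)² + 0.050²] = 0.41, in line with the r = 0.40 row of step 3.

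The 4-hour split loses 4 to 28 points here. The tertile trend loses 3 to 10, except about 1 point where power is already near 100%. With mean 5.5 and SD 1.5, only 16% of patients fall below 4 hours; the split then loses 35 points at 0.063 mm, and continuous power at 0.025 mm is 18%.

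**5. Two changes of assumption.**
- Change SD 0.0707 mm (0.050 × √2, uncorrelated repeat measures): at 0.025 mm, over the same five pairs of hours, power is 13–26% continuous and 9–19% with the 4-hour split, a loss of 4 to 8 points.
- Benefit only at 4 hours or more, same average reduction of 0.025 mm, change SD 0.050 mm: the 4-hour split has 55–97% power and continuous hours 32–86%, so the split leads by 11 to 24 points.

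**The case against.** The strongest reply is that the protocol leaves the form of this analysis open. It does not say that stratification is the only use of compliance, does not exclude hours as a covariate, and fixes neither boundaries nor crossing; such details commonly sit in a statistical analysis plan, which is not at hand. This stands to a degree: a reader might infer that hours will never enter a model, and the text does not go that far. But the protocol does name a method, that method is grouping, and a later plan that follows it would group.

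The reply is also right that 4 hours is a target and not a stated cut, that four cells averaging 16 patients would require a crossing nobody has specified, and that stratifying does not remove the main paired analysis. The point does not rest on any of these.

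Finally, the power gap depends on the shape of the response. A linear truth favours a linear slope, and step 5 shows that a true threshold at 4 hours reverses the ranking. That reversal needs the cut to sit at the true threshold, and nothing in the documents places it there. It is a good reason to check non-linearity and keep the 4-hour table, but not to rely on strata alone.

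**Conclusion.** The point holds as a better use of data already collected. It is not a contradiction or a wrong figure in the protocol. If compliance is cut in two and the response is roughly linear, about 36–46% of the information is lost for splits from 50/50 to 25/75. Under the assumptions of step 4 this is roughly 4–30 points of power, more when few patients fall below the cut, and about 3–12 points with a tertile trend. The distribution of hours, the number and place of cuts, the response shape and the change SD are all assumptions.

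Two stronger readings are tempting and not supported. One is that most of the dose-response information is discarded: that needs a split of about 20/80 or more extreme. The other is that hours of use are the only CPAP contrast inside the study: the before-after comparison is the stated main one, and hours are the only *between-patient* contrast.

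The gain should not be oversold. At the 0.025 mm design effect even continuous hours give only about 21–46% power in the settings tabulated.

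**What to change.** In the treatment-period paragraph of Project 2, replace stratification by compliance with a regression, for example:

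*The 12-month change in each primary outcome (CRAE, CRVE, AVR, IMT) will be regressed on mean nightly CPAP hours over the 12 months, as a continuous variable with zero for nights not used, with the baseline value of the outcome and cardiovascular medication use as covariates. The slope per hour with its 95% CI is the compliance analysis. Non-linearity will be examined with a quadratic or spline term. Results below and above 4 hours per night will be tabulated descriptively.*

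The cost is wording only, since the hours are already downloaded. Three limits belong beside it: the slope assumes approximate linearity; hours are self-selected, so the slope can be confounded, for instance by adherence to other medication, which the protocol also monitors; and power at the design effect is modest, so a wide interval should not be read as absence of a dose-response.

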**Preliminary Data:** We have completed a pilot study in 28 subjects referred for investigation of SDB, with retinal photography performed before and after one night of PSG. Subject characteristics: age  $55.1 \pm 11.9$  years (mean $\pm$ SD); BMI  $34.4 \pm 7.3$  kg/m^2; RDI  $31.7 \pm 24.9$  events/hour (range 0-102); snoring  $49.4 \pm 26.2$  % sleep epochs. The prevalence of retinal emboli was 10.7% (present in 3/28 subjects both pre and post sleep; all 3 with heavy snoring or severe OSAS). This represents an 8-fold increase in prevalence of asymptomatic retinal emboli compared with population data from the local BMES (prevalence 1.4%; 95% CI 1.0 to 1.8%) (42). Overnight, mean retinal arteriolar diameter decreased from  $153.9 \pm 13.5$  to  $151.7 \pm 14.2$   $\mu\text{m}$  ( $p < 0.02$ ); mean venular diameter increased from  $222.9 \pm 23.2$  to  $227.3 \pm 22.5$   $\mu\text{m}$  ( $p < 0.016$ ); and mean AVR fell from  $0.69 \pm 0.06$  to  $0.67 \pm 0.06$  ( $p = 0.001$ ; Fig 1). Correlation analysis (Spearman's) demonstrates significant associations between: (i) increasing snoring time and a decrease in retinal arteriolar diameter ( $r = 0.42$ ,  $p < 0.03$ ; Fig 2); and (ii) overnight oxygen desaturation and decreasing AVR ( $r = 0.38$ ,  $p < 0.05$ ). In the subjects where RDI was  $< 15$  events/hour (control), there was no change in overnight retinal arteriolar or venular diameters ( $p > 0.5$ ). Thus, preliminary data demonstrate that there is: 1) no overnight change (sleep or circadian influence) in retinal microvasculature in control/mild OSAS subjects; 2) a clear overnight increase in venular diameter, and decrease in

arteriolar diameter and AVR in OSAS subjects; 3) a decrease in arteriolar diameter which is associated with increasing snoring time; and 4) an increased prevalence of retinal emboli in OSAS. These are the first data to demonstrate overnight change in the retinal microvasculature.

[figure not shown]

Figure 1: Identity plot of AV Ratio am versus pm. Note that controls (triangles) fall along the identity line; cases (circles) are shifted to the right, consistent with overnight decrease in AVR. Figure 2: Change in arteriolar diameter (pm-am) plotted against snoring. Note the correlation (solid line;  $r=0.38$ ;  $p<0.05$ ) between increasing snoring and decrease in overnight arteriolar diameter.

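### In Project 2 the morning retinal photograph follows an untreated night at baseline and a CPAP night at follow-up, so a 12-month comparison that uses morning readings could show regression that has not occurred

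*Protocol*

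**What the plan says.** All of the following except the pilot is in the Project 2 section of the protocol.

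- **Baseline.** Once risk factors are stable, "diagnostic PSG with repeat carotid Doppler ultrasound (pm) and retinal photography (pm and am) will be performed as a baseline". CPAP starts only after that: "Subjects will then have a laboratory CPAP titration study, to eliminate snoring and obstructive events as per laboratory protocol". The baseline morning photograph therefore follows an untreated night.
- **Follow-up.** "Overnight CPAP review studies using the patient's CPAP treatment pressure will be undertaken at 6 months and one year". The measurements are "Repeat carotid Doppler ultrasound (pm), retinal photography (pm and am), blood pressure (pm and am"), plus fasting bloods and weight. The follow-up morning photograph therefore follows a night on CPAP.
- **Outcomes.** "The primary outcome variables (CRAE, CRVE, AVR and IMT) are objective measures of structural changes", and the protocol adds that they are unlikely to improve spontaneously. It does not say whether the retinal outcome is the evening reading, the morning reading, their mean or the overnight change. Carotid ultrasound is evening only at every Project 2 visit.
- **Interpretation.** The paired comparison is called valid, with "differences between the before and after treatment measures being related to the treatment intervention over 1 year". Under Significance, a rise in CRAE and a fall in CRVE are to be attributed to CPAP.
- **Pilot (Background, Preliminary Data; 28 subjects, one night).** Arterioles narrowed, venules widened and AVR fell overnight. Subjects with RDI below 15 showed no change in either diameter. The protocol comments: "These are the first data to demonstrate overnight change in the retinal microvasculature". The Outcomes paragraph of Project 1 describes the overnight change as an acute effect of sleep-disordered breathing and treats chronic change as a further question.

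**The concern.** Morning readings at baseline and at 12 months differ in two ways: a year of therapy, and whether the night just before the photograph was treated. The protocol's own pilot says the second difference alone moves the outcome. For morning readings, then, the statement that these variables "are objective measures of structural changes which are unlikely to spontaneously improve without intervention" conflicts with the pilot: part of the before/after difference can be the absence of one night's acute effect.

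The bias runs in the favourable direction. Preventing the overnight shift gives a wider CRAE, a narrower CRVE and a higher AVR, which is the pattern the protocol would read as regression of disease. Project 2 has no control arm, so no other comparison in the study would expose the artefact. At stake is the central retinal claim, lasting regression over 12 months.

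**Working it through.** **Inputs from the protocol**

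- Pilot, evening to morning: CRAE 153.9 to 151.7 µm (p < 0.02); CRVE 222.9 to 227.3 µm (p < 0.016); AVR 0.69 to 0.67 (p = 0.001).
- Benchmark for a relevant arteriolar change: 3.5 µm per year (Project 2).
- Completers: 64 of 80 after 20% drop-out (Project 2). Two-sided alpha 0.05.
- Cross-sectional SD of CRAE: 13.6 µm (Project 1 sample size).

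**Reproducing the plan's figures**

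- AVR from the mean diameters: 153.9/222.9 = 0.690 and 151.7/227.3 = 0.667, matching the reported 0.69 and 0.67.
- Sample size: a two-group t-test with difference 0.025 mm and SD 0.050 mm needs 63.8, so 64, per group (power 80.1%), and 64/0.8 = 80. That calculation concerns IMT. Here 64 is used only as the number of completing pairs.

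**Size of the artefact with zero structural change, if CPAP abolishes the whole pilot shift**

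| Comparison, 12 months minus baseline | CRAE | CRVE | AVR |
|---|---|---|---|
| Morning − morning | 153.9 − 151.7 = +2.2 µm | 222.9 − 227.3 = −4.4 µm | 0.69 − 0.67 = +0.02 |
| Mean of evening and morning | +1.1 µm | −2.2 µm | about +0.01 |
| Evening − evening | no test-night component | none | none |

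For CRAE, 2.2/3.5 = 63% of the protocol's benchmark.

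**Chance that this alone is significant.** The test is a paired t-test with n = 64 and noncentrality shift/(SD/√64). The protocol gives no SD for the 12-month change, so it is assumed. The lower end, 5 µm, is close to the largest one-night SD that the pilot p-value allows: 2.2 × √28/2.473 = 4.7 µm. The upper values follow from SD of change = 13.6 × √(2(1 − r)), with assumed one-year correlations r = 0.8, 0.7 and 0.5 giving 8.6, 10.5 and 13.6 µm.

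| Assumed SD of CRAE change (µm) | Noncentrality, morning readings | Morning readings | Evening/morning mean |
|---|---|---|---|
| 5 | 2.2/0.625 = 3.52 | 93% | 41% |
| 7.5 | 2.35 | 64% | 21% |
| 8.6 | 2.05 | 52% | 17% |
| 10 | 1.76 | 41% | 14% |
| 10.5 | 1.68 | 38% | 13% |
| 13.6 | 1.29 | 25% | 10% |

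For CRVE on morning readings (shift 4.4 µm), the chance is 93%, 64% and 41% for an assumed SD of 10, 15 and 20 µm. All of these exceed the nominal 5%.

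**The case against.** **The choice of reading may simply be left to the SAP.** Nothing in the protocol says that morning or pooled values will be used for the 12-month comparison. Evening photographs are taken at every visit, and an evening-to-evening comparison avoids the test-night problem. Project 1 uses the morning reading to obtain overnight change, and Project 2 takes its procedures from Project 1. This stands as a limit: the bias is conditional on the reading chosen. It does not dispose of the point, because the protocol makes a positive claim, that these outcomes are structural and the paired comparison valid, and its own pilot contradicts that claim for morning readings.

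**The high probabilities need a small SD.** This stands. An SD of 5 µm over a year is optimistic when the pilot already allows up to 4.7 µm over one night. The whole range has to be reported, and every figure assumes that CPAP removes all of a shift estimated in 28 people. In the other direction, the pilot mean includes subjects with RDI below 15 who showed no change, while Project 2 enrols RDI above 30, so the shift there may be larger.

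**Three stronger readings are tempting but not supported.**

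- A reader might infer that every primary outcome is affected. IMT, the only outcome used to size Project 2, is measured in the evening only and is not exposed. AVR is computed from CRAE and CRVE, so it is not a third independent signal.
- A reader might extend the point to Project 1's cross-sectional comparison. Project 1 has no treated night, so the asymmetry does not arise there.
- A reader might take the evening comparison to be free of all short-term effects. Follow-up evening readings come hours after treated nights at home and baseline ones after untreated nights. The protocol does not say how long the overnight shift lasts.

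**Conclusion.** The point holds in conditional form. Project 2 compares morning photographs taken after an untreated night with morning photographs taken after a CPAP night. It describes the retinal outcomes as structural and does not confine the comparison to evening readings. By the protocol's own pilot, a comparison on morning readings could show CRAE +2.2 µm, CRVE −4.4 µm and AVR +0.02 with no regression at all, and half of that on the evening/morning mean.

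With 64 pairs, the chance of a significant CRAE gain from this alone is about 93% to 25% on morning readings and 41% to 10% on the mean. This rests on two assumptions: that CPAP abolishes the whole pilot shift, and that the SD of 12-month change lies between 5 and 13.6 µm. The documents do not show that morning readings will be the ones analysed, so this is a risk the plan leaves open and not an error already made. It should be closed before analysis because the bias is favourable and there is no control arm to reveal it.

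**What to change.** In Project 2:

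1. State that the primary 12-month retinal comparison (CRAE, CRVE, AVR) is the 12-month evening reading minus the baseline evening reading.
2. Analyse the overnight change (morning minus evening) at each visit separately, as the acute effect of CPAP.
3. Limit the statement that the retinal outcomes are structural, and the attribution of differences to a year of treatment, to the evening comparison. Acknowledge that carry-over from recent treated or untreated nights into the evening reading cannot be excluded.

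The cost is a few sentences, since every photograph is already scheduled. The downsides are that morning readings no longer add precision to the primary comparison and that the possible carry-over remains as a stated limitation.

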***If OSAS constitutes an independent stimulus to the development of cerebral microvascular and macrovascular disease, it is plausible that removal of this stimulus with CPAP therapy may also be associated with regression of the early changes of vascular disease*** within the six to twelve month time frame. In support of this, a recent study by Drager et al (15) demonstrated that effective treatment of a group of 12 severe, hypoxic OSAS patients with CPAP for 4 months resulted in a significant decrease in carotid IMT of 0.063mm, compared with a small increase of 0.008mm in 12 control OSAS subjects. Overall, this represented a 9% reduction in IMT over only a four month treatment period. This study provides strong support that CPAP treatment is able to significantly reduce the severity of cerebral macrovascular disease within a reasonable timeframe. We propose to test this proposition in order to establish the benefits of CPAP treatment in terms of both cerebral microvascular and macrovascular risk reduction in patients with OSAS.

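### Project 2's 80% power is calculated for a two-group t-test, but the study is one arm compared with itself; the calculation should be restated as paired, with the SD of change given

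*Protocol*

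**What the plan says.** Under Project 2, Statistical Analysis and Sample Size, the protocol gives the number of patients as a "sample size of 64". The method behind it is stated as follows: "assuming that the common standard deviation is 0.050 mm and using a two group t-test with a 0.05 two-sided significance level". The effect size is an IMT difference of 0.025 mm at 12 months, with 80% power. On attrition the paragraph says: "We will study 80 subjects to allow for a 20% drop-out rate".

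The same project's Design paragraph describes a "one-year prospective, longitudinal, observational study of OSAS patients (acting as their own controls". The later paragraph that defends having no untreated arm says: "This will enable a valid paired comparison with the differences between the before and after treatment measures". All 80 patients receive CPAP and there is no second group.

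To support the size, the sample-size paragraph cites an earlier CPAP study: "Given the demonstrated reduction in IMT of 9% (0.063 mm) in 24 patients over only four months". The Background section on IMT describes the same reference as "effective treatment of a group of 12 severe, hypoxic OSAS patients with CPAP for 4 months", with a fall of 0.063 mm, against 12 control patients whose IMT rose by 0.008 mm.

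**The concern.** The sample size comes from a test that the study will not run. A two-group t-test compares two sets of independent patients, and its power depends on the SD between patients within a group. A before/after comparison in one cohort is a one-sample test on each patient's change. Its power depends on the SD of that change or, equivalently, on the per-visit SD and the correlation between visits.

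The protocol gives one SD, calls it common, and does not say which of these quantities it is. The source it names for the power analysis is not reproduced in enough detail to settle this. IMT is one of the four primary outcome variables and the only one with a numerical power calculation in Project 2. What is at stake is whether the 80% claim can be relied on for the analysis that will be reported.

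**Working it through.** **Inputs.** From the sample-size paragraph: difference 0.025 mm, SD 0.050 mm, two-sided alpha 0.05, power 80%, n = 64, drop-out 20%. From the Design paragraph and the defence of the single arm: one arm, paired comparison. The correlations (rho) and the alternative SDs of change below are assumptions, because the protocol gives none. Power is from the noncentral t distribution.

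**1. Reproducing the plan's figure.** Standardised difference = 0.025 / 0.050 = 0.5. An independent two-group t-test at two-sided 0.05 with 80% power needs 63.8, so 64 per group (128 in all). Power at 64 per group is 80.1%. The figure of 64 is thus reproduced as a per-group number. Drop-out: 64 / (1 - 0.20) = 80, which agrees with the protocol. The per-group number has become the size of the whole one-arm study.

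**2. The planned test.** For a paired t-test on n = 64 completers, the noncentrality is 0.025 / (SD of change / sqrt(64)) = 0.025 x 8 / SD of change, with 63 degrees of freedom.

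*Reading A: 0.050 mm is the SD of the 12-month change.* Noncentrality = 0.2 / 0.050 = 4.0. Power is 97.6%. The change detectable with 80% power is 0.018 mm, and 34 pairs would give 80% power for 0.025 mm.

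*Reading B: 0.050 mm is the SD at each visit.* SD of change = 0.050 x sqrt(2(1 - rho)).

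| rho (assumed) | SD of change, mm | Power, 64 pairs | Pairs for 80% |
|---|---|---|---|
| 0 | 0.0707 | 79.5% | 65 |
| 0.25 | 0.0612 | 89.5% | 50 |
| 0.5 | 0.0500 | 97.6% | 34 |
| 0.7 | 0.0387 | 99.9% | 21 |

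At rho = 0 the noncentrality is 0.2 / 0.0707 = 2.83. The two-group test with 64 per group gives the same value: 0.025 / (0.050 x sqrt(2/64)) = 2.83. The plan's calculation is therefore, in effect, the paired one with the correlation set to zero. The small gap between 79.5% and 80.1% comes from the degrees of freedom (63 against 126).

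**3. Where power would fall short.** Taking the SD of change directly, with 64 pairs and 0.025 mm:

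| SD of change, mm (assumed) | Power |
|---|---|
| 0.05 | 97.6% |
| 0.06 | 90.7% |
| 0.07 | 80.3% |
| 0.08 | 69.2% |
| 0.10 | 50.4% |

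The break-even SD of change is 0.0703 mm. With a per-visit SD of 0.050 mm, an SD of change of 0.08 mm would need 1 - rho = 0.08^2 / (2 x 0.050^2) = 1.28, that is, rho = -0.28. A real shortfall would therefore require 0.050 mm itself to be too small, or a negative correlation between a patient's two readings.

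**4. The supporting study.** The Background gives 12 treated and 12 control patients (24 in all), and the 0.063 mm fall belongs to the 12 treated. The sample-size paragraph attaches that fall to 24. Neither 0.063 mm nor 24 enters the calculation in step 1.

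**The case against.** The strongest reply is that the slip does no harm. If before and after are treated as the two groups, the study has 64 values in each, and ignoring the pairing can only understate power while the correlation is positive. Under either reading of 0.050 mm the paired power is about 80% or higher, and the protocol itself describes its calculation as conservative. This largely stands and limits how serious the point is. It does not make the stated power that of the planned test, and it relies on an SD whose meaning is not given.

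A reader might infer three stronger things, none of which the documents support:

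- That 64 means 32 + 32, giving 50.4% power in a two-group test. Nothing in the protocol splits the patients this way, and the Design paragraph excludes it.
- That 128 patients are needed. That number belongs to two independent groups, which Project 2 does not have.
- That neither the detectable change nor the tolerance for drop-out can be known. On the plan's own SD, the detectable change for 64 pairs is 0.018 mm (Reading A), or at most 0.0251 mm (Reading B, any non-negative correlation). The 20% allowance reproduces exactly. What is missing is a justified SD of change.

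**Conclusion.** Wrong as written, and should be fixed. The 80% power belongs to a two-group t-test with 64 per group, whereas Project 2 is a paired comparison in one arm with 64 expected completers. For 0.025 mm, the paired power is 98% if 0.050 mm is the SD of change, and about 80% to 98% for correlations from 0 to 0.5 if it is the per-visit SD (assumed equal at both visits). It drops below 80% only if the SD of change exceeds about 0.07 mm, for example to 69% at 0.08 mm, and nothing in the protocol points to a value that high. The finding does not show an underpowered study. The error is probably conservative and implies no extra patients.

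The figure of 24 patients contradicts the Background. This is minor: it affects only the sentence that calls the sample size robust.

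**What to change.** Replace the two-group sentence with a paired calculation (one-sample t-test on the 12-month change, two-sided 0.05) for 64 completers. State and source the SD of change or, failing that, the per-visit SD and the between-visit correlation. Do not simply carry 0.050 mm over as the SD of change and claim 98% power, because the protocol does not establish that meaning.

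Alongside the sourced value, show power for 0.025 mm over a range labelled as assumed: 98% at an SD of change of 0.05 mm, 91% at 0.06, 80% at 0.07 and 69% at 0.08. Keep the 20% drop-out allowance and the total of 80, unless the sourced SD turns out to be above about 0.07 mm.

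In the same paragraph, correct the description of the supporting study to 12 CPAP-treated patients with 12 controls, in line with the Background.

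Cost: one paragraph reworded, plus the work of finding a source for the SD. On the plan's stated SD there is no change to recruitment, visits or analysis.
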